#### **9.1.2.2 Provisional inclusions:**

*Current psychotherapy:* If a patient is currently participating in psychotherapy in the community, the potential subject will be referred back to the outpatient provider(s) to fully discuss the pros and cons of terminating treatment for purposes of study enrollment.

*Recent medication change:* Subjects who changed their psychotropic medication in the last 8 weeks, but are otherwise eligible may enroll pending another SCID interview when they have stabilized on their medications.

*Current panic, PTSD, OCD:* Patients may return for assessment if these conditions are successfully treated or spontaneously remit.

#### **9.1.3 Exclusion Procedures:**

If the subject does not meet entry criteria, and is unlikely to in the future, they may receive a list of local providers or and/or other possible treatment studies.

*Active suicidal ideation:* If the participant is excluded because of active suicidal ideation, follow the suicide assessment procedure in the "Managing Suicidality" manual.

### **9.2 Informed Consent**

If the subject meets entry criteria,, **they will undergo the following informed consent procedures:**

**1) Briefly, describe the study, including:**

- Timeline and procedure**

- Risk and benefits and alternative treatments**

- **the decision to not participate or to withdraw from the study will not adversely affect current or future interactions with the Neurodevelopment Center or Brown University.**

2) Provide a copy of the IRB-approved consent form and allow them to read and ask questions.

3) Then quiz the subject via open-ended questions about important aspects of the study protocol to assess his/her understanding of study procedures. For example, “What kind of treatment

would you receive if you take part in this study?” Acceptable answer: “Mindfulness Meditation training for 8 weeks.” If the patient answers incorrectly, the interviewer will review the relevant section of the consent form again and query the patient until (s)he can provide an appropriate response, in a process called iterative feedback.

### 9.3

### **Baseline Assessment**

Subjects complete baseline questionnaires and laboratory assessments at the Neurodevelopment Center. See Procedures Manual for Details.

### 9.4 **Enrollment**

Formal enrollment in the study requires the following:

- 1) Meet all entry criteria after screening
- 2) Completed informed consent procedures
- 3) Completed all baseline assessments (both self-report and laboratory assessment)
- 4) Continued interest and availability to continue the study after completing #1-3
- 5) Completion of treatment randomization procedures

### 9.5 **Treatment Randomization**

Within 1 month of the first completed baseline assessment, if at least 3 other participants have completed assessment (total of 4), proceed to randomization to choose a treatment. See Treatment Randomization for procedure.

### 9.6 **Treatment**

Participants enter one of three active treatments for 8 weeks. See [Treatment Section](#). And treatment manuals

### 9.7

### **Post Treatment Assessment**

After the 8th class, participants repeat the baseline assessment procedures (sleep diaries, z-machines, self-report questionnaires and laboratory assessments).

In addition to outcome questionnaires, participants will also complete questionnaire to their experience of the therapist and the treatment experience. See section on [Therapist Adherence](#)

### 9.8

### **Assessment**

### **3 Month Follow-up**

Three months after the post-treatment assessment, the participants returns for an in-person clinical assessment interview (IDS, PANAS, DASS, WBS). The participant will also complete a

3rd set of self-report questionnaires. For details, see Table 2.1 Timeline and Summary of Assessments in the Procedures Manual.

## **9.9 Adverse effects**

Patients who exhibit clinical deterioration (an increase in IDS score of > 16 points) or Non-responders (identified as minimal change in symptoms from baseline assessment) will be assessed for safety and provided with appropriate clinical follow-up, including referrals to other treatment, if desired.

Patients who express active suicidal ideation (IDS 18=3) will be followed with the suicidality management procedure (described in detail in the Procedures Manual Safety Section) and monitored until resolution.

### **9.9.1 Stopping Rules for an Individual Participant**

A study participant will be discontinued from further Study Intervention(s) if:

- Any clinical adverse event, laboratory abnormality, intercurrent illness, other medical condition or situation occurs such that continued participation in the study would not be in the best interest of the participant.

Development of any exclusion criteria may be cause for discontinuation.

Participant will continue to be followed with participant's permission if Study Intervention is discontinued.

## **10. ASSESSMENT OF SAFETY**

### **10.1 Ethics/Protection of Human Subjects**

#### **10.1.1 Institutional Review Board/Ethics Committee**

The above protocol is subject to review and approval by the Brown University Institutional Review Board (IRB) prior to the implementation of the protocol. Any amendments to the protocol or consent materials must also be approved before they are placed into use.

#### **10.1.2 Informed Consent Process:**

Written informed consent will be obtained from each subject at entry into the study. Informed consent is obtained by the following process:

1. The subject will be asked to review the study consent form.
2. The PI or Co-Investigator (Co-I) will meet with the subject to review the form, to confirm the subject's understanding of the study, and to answer any questions that the subject might have.
3. Once the subject demonstrates understanding of the study and agrees to participate in the study, the consent will be signed in the presence of eligible study staff.

### **10.1.3 Adherence**

The Study Protocol for the **K23 AT006328-01A1** will adhere to the protocol approved by the Brown University IRB. Major modifications to the IRB protocol that are considered a change in scope, the scientific intent, study design, patient risk, or human subject protection (i.e. change in control group) will be discussed with appropriate NCCAM officers prior to implementation. Minor modifications that are considered editorial or administrative updates (i.e. address changes) do not need prior approval "as long as the change does *not* affect the scientific intent, study design, patient risk, or human subject protection" (NCCAM 2012, Guidance on Changes in Clinical Studies in Active Awards – When is Prior NCCAM Approval Required?)

### **10.1.4 Attached IRB Documents:**

The following documents are included in the Regulatory Binder.

- Brown IRB approval
- IRB-approved Consent Form

## **10.2 ADVERSE EVENTS**

### **10.2.1 Definition of an Adverse Event (AE)**

"An adverse event (AE) is any untoward medical occurrence in a subject temporally associated with participation in the clinical study or with use of the experimental agent being studied. An adverse finding can include a sign, symptom, abnormal assessment (laboratory test value, vital signs, electrocardiogram finding, etc.), or any combination of these."

### **10.2.2 Definition of a Serious Adverse Event (SAE)**

Serious Adverse Event (SAE): A Serious Adverse Event is defined as an AE meeting one of the following conditions:

- Death
- A life-threatening event
- Inpatient hospitalization or prolongation of existing hospitalization
- A persistent or significant disability/incapacity
- A congenital anomaly or birth defect

- Important medical event based upon appropriate medical judgment”

#### 10.2.2.1 AE/SAE Severity

- **Grade 1 (Mild):** *events require minimal or no treatment and do not interfere with the patient’s daily activities.*
- **Grade 2 (Moderate):** *events result in minor inconvenience or concern with the therapeutic measures. Moderate events may cause some interference with functioning.*
- **Grade 3 (Severe):** *events interrupt a patient’s usual daily activity and may require systemic drug therapy or other treatment. Severe events are usually incapacitating.*
- **Grade 4 (Life threatening):** *Any adverse drug experience that places the patient or participant, in the view of the investigator, at immediate risk of death from the reaction as it occurred, i.e., it does not include a reaction that had it occurred in a more severe form, might have caused death.*
- **Grade 5 (Death)**

#### 10.2.2.2 Relationship of AEs/SAEs to the Study Intervention

*This designation will be made by the principal investigator.*

AEs will be categorized according to the likelihood that they are related to the study intervention. Specifically, they will be labeled definitely unrelated, definitely related, probably related, or possibly related to the study intervention.

##### **Definitely Related**

There is clear evidence to suggest a causal relationship, and other possible contributing factors can be ruled out. The clinical event, including an abnormal laboratory test result, occurs in a plausible time relationship to study agent/intervention administration and cannot be explained by concurrent disease or other drugs or chemicals. The response to withdrawal of the study intervention should be clinically plausible. The event must be phenomenologically definitive, with use of a satisfactory rechallenge procedure if necessary.

##### **Probably Related**

There is evidence to suggest a causal relationship, and the influence of other factors is unlikely. The clinical event, including an abnormal laboratory test result, occurs within a reasonable time sequence to administration of the study agent/intervention, is unlikely to be attributed to concurrent disease or other drugs or chemicals, and follows a clinically reasonable response on withdrawal (dechallenge). Rechallenge information is not required to fulfill this definition.

##### **Possibly Related**

There is some evidence to suggest a causal relationship (e.g., the event occurred within a reasonable time after administration of the trial medication). However, the influence of other factors may have contributed to the event (e.g., the subject's clinical condition, other concomitant events). Although an adverse drug event may rate only as "possible" soon after discovery, it can be flagged as requiring more information and later be upgraded to probable or certain as appropriate.

### **Unlikely**

A clinical event, including an abnormal laboratory test result, whose temporal relationship to study agent/intervention administration makes a causal relationship improbable (e.g., the event did not occur within a reasonable time after administration of the trial medication) and in which other drugs or chemicals or underlying disease provides plausible explanations (e.g., the subject's clinical condition, other concomitant treatments).

### **Not related**

The AE is completely independent of study study agent/intervention administration, and/or evidence exists that the event is definitely related to another etiology. There must be an alternative, definitive etiology documented by the clinician Expected Events Related to Disease Process: Provide explicit definitions of the type(s), grade(s), and duration(s) of adverse event(s) that will be considered disease related.

#### **10.2.2.3 Expected Risks -NCCAM statement**

The following is a statement from NCCAM about the safety profile of meditation practice:  
Side Effects and Risks of Meditation

*Meditation is considered to be safe for healthy people. There have been rare reports that meditation could cause or worsen symptoms in people who have certain psychiatric problems, but this question has not been fully researched. People with physical limitations may not be able to participate in certain meditative practices involving physical movement. Individuals with existing mental or physical health conditions should speak with their health care providers prior to starting a meditative practice and make their meditation instructor aware of their condition.*

SOURCE: <http://nccam.nih.gov/health/meditation/overview.htm#sideeffects> (Oct 26,2011)

#### **Expected risks to the subject are as follows:**

Discomfort during meditation: Meditation-based interventions may results in discomfort with attention to unpleasant thoughts, feelings or body sensations. Some individuals may experience an initial increase in undesirable emotions with increased attention to them.

Discomfort during assessments: Some participants may feel uncomfortable answering personal questions about their psychological health. The physiological recording electrodes may cause mild skin irritation. Some of the stimuli may be unpleasant or graphic.

Risk of adverse events during the study. It is possible that some patients will have an adverse event during the study, including failure to respond to treatment, worsening of depressive symptoms, suicidal ideation or behavior, or other adverse events.

#### 10.2.2.4 Impact statement

:

**“These risks are considered to be minimal and are addressed in the protocol and consent form.”**

#### 10.2.2.5 Measures that will be taken to minimize study risk:

Meditation-related discomfort: Regarding psychological discomfort associated with mindfulness practice, participants are self-guided and are encouraged to set their own limitations. In addition, the curriculum of the training program is specifically geared towards dealing with such discomfort.

Assessment-related discomfort: None of the assessment procedures pose a serious risk to volunteers. With regard to the collection of polysomnographic data, procedures that are standard in [name] Sleep Research Laboratory will be used. These procedures have been used with hundreds of participants, with no reports of death or injury attributed to the procedures. [name] group has reported minor skin irritations from tape placed on the face in a minority of cases. For the EEG/EMG recordings, precautions such as using latex-free or micropore tape and conductant paste (instead of glue) to affix electrodes will be taken. The clinician rating and self report measures are commonly used for research and clinical purposes. There are no known risks attendant to its administration. Well-documented procedures for eliciting emotion are used, there are no known risks associated with these procedures.

#### 4) Adverse events:

Clinical Deterioration and Suicidality: Participants assigned to any treatment group may experience significant clinical deterioration or suicidal ideation. All patients will be monitored by study staff at weekly intervals in person or by telephone and assessed every two weeks with questionnaires about mood and affect. [name] and [name] are licensed clinical psychologists and have extensive experience evaluating research participants for clinical deterioration or suicidality. Significant risk for suicide will be defined by an IDS item 18 score = 3, or the report of a desire or intent to hurt oneself to any member of the study staff. At follow-up, study staff may also identify participants with significant clinical deterioration (as defined by an IDS score > 40 (which is equivalent to a 17-item Hamilton Rating Scale for Depression (HRSD) score > 20) or an increase in IDS score of > 16 points, which is equivalent to an increase in HRSD score of > 8 points. If study staff identify an individual with significant clinical deterioration or who report any suicidal ideation, we will utilize our standard protocol for managing these problems. Study staff will immediately contact [name] or [name], who will evaluate the patient over the telephone or in person. First, they will conduct a suicide risk assessment to determine whether it is necessary to take immediate action to prevent the participant from causing harm to herself. If needed, actions that Drs. [name] or [name] may take include having a family member bring the person to Butler Hospital or sending an ambulance so that the individual may be evaluated for inpatient psychiatric admission. For detailed procedures,

please see Procedures Manual: Manual for Managing Suicidal Ideation and Behavior and Psychiatric Hospitalization Procedures. If the study participant has experienced significant deterioration, but is not in immediate danger of hurting herself, we will take the following actions. First, we will inform the patient about procedures for contacting emergency services should they find themselves at risk for self-harm. Second, with the patient's knowledge, we will contact their primary care provider to inform them of the deterioration. We will urge the patient to make an appointment with that provider. Third, if the patient consents, we will speak with one of their family members to ensure that she is aware of the seriousness of the patient's symptoms and the agreed-upon treatment plan. We will provide psychotherapy referrals if the patient wishes them. Participants who a) require an inpatient psychiatric admission; or b) begin antidepressants or psychotherapy while in the study will be officially discontinued from the study at that point. We will collect endpoint data at the point of discontinuation. Depending on reasons for discontinuation and our clinical judgment, participants may be allowed to finish out their time in the meditation class.

Non-Response to Treatment: Independent of clinical deterioration, the possibility that the treatment will not yield benefit is another possible risk and will be explained during informed consent procedures. All patients will be monitored by study staff in person or by telephone at weekly intervals and assessed every two weeks with questionnaires about mood and affect. Non-responders (identified as minimal change in symptoms from baseline assessment) will be provided with referrals to other treatment, if desired.

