### 6.2 Inclusion Criteria:

Participants must meet the following requirements to participate in the study

- English-speaking
- ages 18-65
- mild-severe levels of depression (IDS 10-48) or high level of negative affect (PANAS negative affect scale >20 in last month).
- May include the following DSM diagnoses and classifications of emotional disturbances:  
296.xx Major Depressive Disorder, single episode or recurrent, chronic, or in partial remission;  
300.4 Dysthymic Disorder;  
311 Depressive Disorder NOS (minor depression and recurrent brief depressive disorder;  
300.2 Generalized Anxiety Disorder;  
293.84 Anxiety Disorder Due to a Medical Condition;  
300.00 Anxiety Disorder NOS.

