## 10.3 Data Collection Procedures for Adverse Events

### 10.3.1 Scheduled collection

#### (IDS interviews):

Item 18 =3 (suicidal ideation)

IDS total has increased >16 points since the last assessment

OR IDS total score is > 48

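### Three sections use different IDS rules for worsening, and the IDS >40 rule in section 10.2.2.5 can label a patient who entered at 41-48 and did not worsen as significantly deteriorated

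*Protocol*

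**What the plan says.** The protocol sets IDS limits for worsening in three places.

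- **Section 9.9** uses change only: "Patients who exhibit clinical deterioration (an increase in IDS score of > 16 points". It also says "Non-responders (identified as minimal change in symptoms from baseline assessment) will be assessed for safety and provided with appropriate clinical follow-up".
- **Section 10.2.2.5, item 4**, adds an absolute limb. At follow-up, staff may identify "significant clinical deterioration (as defined by an IDS score > 40", or a rise of more than 16 points. For a patient not in immediate danger, the listed steps include "we will contact their primary care provider to inform them of the deterioration", with the patient's knowledge. The same item then treats non-response as a separate matter: "Independent of clinical deterioration, the possibility that the treatment will not yield benefit is another possible risk". The response there is referral if the patient wants it.
- **Section 10.3.1** lists the IDS results that are collected as adverse events and does not use the word deterioration. Apart from the suicidality item, the triggers are "IDS total has increased >16 points since the last assessment" and "OR IDS total score is > 48".

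Entry under section 6.2 is by "mild-severe levels of depression (IDS 10-48") or, alternatively, by high negative affect on the PANAS. Section 6.3 excludes only scores above 48.

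**The concern.** Deterioration is a change from where the patient started. The 40-point limb measures severity: section 10.2.2.5 justifies it by an equivalent Hamilton score, not by a change. Because the cut lies inside the eligible range, some patients meet it on the day they enter. If such a patient returns at the same score or a lower one, section 10.2.2.5 calls this significant deterioration, section 9.9 does not, and 10.3.1 records nothing on the IDS rule. An unchanged patient is then also a non-responder, a category that the same section sets apart and handles more lightly.

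The disagreement also runs the other way. A patient who goes from 30 to 46 has worsened by 16 points. That is significant deterioration under 10.2.2.5, but it is not deterioration under 9.9 and does not meet the IDS trigger in 10.3.1.

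What is at stake is that staff working from different sections label the same patient differently, and that a primary care provider may be told of a deterioration in someone who is unchanged or better.

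**Working it through.** No figure in the plan is being reproduced. The check compares the three rules over the eligible scores.

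**Inputs.** Entry score e runs from 0 to 48, which is 49 values: the ceiling comes from sections 6.2 and 6.3, and scores below 10 are possible through the PANAS route. Follow-up score is f. Scores are taken as integers and the rise is taken from baseline. Section 5.2 lists clinical interviews only before treatment and at 3 months, so on that schedule the last assessment is the baseline.

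**Lowest follow-up score that triggers each rule.**

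- 9.9: e + 17
- 10.2.2.5: min(41, e + 17)
- 10.3.1: min(49, e + 17)

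**Agreement.**

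- e = 0 to 24 (25 scores): all three agree, since 24 + 17 = 41.
- e = 25 to 32 (8 scores): 9.9 and 10.3.1 agree, and 10.2.2.5 triggers earlier, at 41.
- e = 33 to 48 (16 scores): all three differ.

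25 + 8 + 16 = 49. Sections 9.9 and 10.2.2.5 differ for 8 + 16 = 24 entry scores.

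**Rise needed under 10.2.2.5**, min(41, e + 17) − e: 17 for e up to 24, 16 at e = 25, 8 at 33, 1 at 40, 0 at 41, and −7 at 48. Under 9.9 it is always 17.

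**Pairs labelled deteriorated without worsening** (f ≤ e and f > 40): for each e from 41 to 48 there are e − 40 such values of f, so the total is 1 + 2 + … + 8 = 36. Of these, 8 have f = e and 28 have f < e. The largest improvement still labelled is 48 − 41 = 7 points.

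**Pairs labelled only through the 40-point limb that do show worsening** (f from 41 to 48, rise 1 to 16): each of the 8 follow-up scores has 16 possible entry scores, so 8 × 16 = 128.

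**Examples, with the rule proposed below in the last column.**

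| Entry to follow-up | Change | 9.9 | 10.2.2.5 | 10.3.1 | Proposed |
|---|---|---|---|---|---|
| 44 to 44 | 0 | no | yes | no | no |
| 48 to 41 | −7 | no | yes | no | no |
| 30 to 46 | +16 | no | yes | no | yes |
| 33 to 48 | +15 | no | yes | no | yes |
| 40 to 49 | +9 | no | yes | yes | yes |
| 24 to 41 | +17 | yes | yes | yes | yes |

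**The case against.** The best defence is that this is a deliberately cautious safety net. Section 10.2.2.5 says staff may identify such patients, and a licensed psychologist then evaluates them. Contact with the provider follows that evaluation and happens with the patient's knowledge. The rules for the label are nested: every patient caught by 9.9 is caught by 10.2.2.5. An unchanged patient at 41-48 is assessed for safety under 9.9 anyway, as a non-responder. Over-triggering in a safety section does less harm than under-triggering.

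All of that stands, and it limits the weight of the point. It does not remove it: a score that has not risen is still defined as deterioration, against the section's own non-response category.

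A reader might infer more than the text supports:

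- *That safety counts or adverse-event data are contaminated.* The protocol plans no count of deteriorated patients, and 10.3.1, which sends IDS results to the adverse-event record, does not use the 40-point cut.
- *That mislabelled patients are removed from the study or denied care.* Under 10.2.2.5 discontinuation follows psychiatric admission or starting antidepressants or psychotherapy, not the label. The extra label brings more attention, not less.
- *That real worsening such as 30 to 46 goes unrecorded.* Only the IDS trigger misses it. Practice logs, direct observation, the 3-month interview and unscheduled reports remain as routes.

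**Conclusion.** The point holds as an inconsistency of definition. Three sections give three IDS rules, and the 40-point limb in 10.2.2.5 lacks a baseline condition that the entry range makes necessary. Its reach is 36 non-worsening score pairs, all with entry at 41-48, plus differing triggers in 9.9 and 10.2.2.5 for the 24 entry scores from 25 to 48.

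These figures count integer scores. The protocol gives no distribution of entry IDS, so they cannot be turned into a number or proportion of patients. They also assume that the rise is measured from baseline; the full assessment timetable is in the Procedures Manual, which is not shown.

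This is a minor-to-moderate correction to safety wording. It affects no endpoint, analysis or stopping rule.

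**What to change.** 1. In 9.9 and 10.2.2.5, use one definition of clinical deterioration: a rise of more than 16 points, or IDS above 40 with a score above that patient's baseline.
2. Align the adverse-event trigger in 10.3.1 to it. Nothing collected now is lost: a score above 48 is always above both 40 and baseline, because IDS above 48 is excluded at entry. Keep the comparison with the last assessment and add a comparison with baseline.
3. Keep IDS above 40 without worsening as a severity prompt for clinician evaluation and referral, not labelled deterioration. Everyone evaluated under 10.2.2.5 today is then still evaluated.

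This removes the label from all 36 non-worsening pairs and keeps it, with its follow-up steps, for all 128 worsening pairs. Replacing the 40-point limb by the 48-point one would also remove the 36, but it would strip the label from the 128; 33 to 48, a 15-point rise, is one of them.

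**Cost.** Wording edits in three sections, and somewhat more IDS-triggered adverse-event entries, since the 128 pairs now meet the trigger in 10.3.1. For entry at 41-48 a one-point rise would suffice. If the clinicians find that too sensitive, they may set a minimum rise of m points (1 to 16) for the 40-point limb. That keeps 8 × (17 − m) of the 128 pairs; the choice of m is clinical.
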